## Abstract

**Objectives::**

The current Indian scenario follows the western cardiac rehabilitation protocol; hence the primary aim of the study is to develop a cardiac rehabilitation phase 1 protocol for the Indian scenario. The protocol will be used in the study as standard rehabilitation protocol for the intervention groups. The literature suggests the use of Pranayama and chair aerobics to improve the anxiety in CABG patients. This study also aims to provide the answer for the effect of Pranayama and chair aerobics on anxiety and exercise tolerance in CABG patients. And also try to find out which among the two intervention is superior among one another.

**Results::**

The data will be analysed using unpaired t test, p value <0.05 will be considered significant.

**Conclusion::**

The result will give a new insight into the field of cardiac surgery, where the effect of pranayama and chair aerobics on anxiety and functional outcome will be proved.

**CTRI registration::**

This trial is prospectively registered in CTRI, the registration number of the trial is **CTRI/2021/09/037008**.

**Highlights::**

**What is already known about this subject?** The effect of Pranayama and chair aerobics on various components like pain, peak expiratory flow after CABG is proven in different studies. The phase 1 cardiac rehabilitation is practiced and adopted from western protocol.

**What does this study add?** The study will give a new insight into the field of cardiac rehabilitation. Definite phase I cardiac rehabilitation protocol for Indian population is not exist in the literature. The Indian set up is using the western protocol, which is not suitable for the Indian population hence could not achieve the expected outcome on discharge. We believe that this study will provide a definite phase I cardiac rehabilitation protocol for the Indian population. This can be followed in the community. Also, this study aims to explore the unexplored area of anxiety after CABG. Where the effect of the Pranayama and chair aerobics will be identified. And also give idea about which treatment technique is superior, and feasible for the patients.

**How might this impact on clinical practice?** The study will provide a new phase I cardiac rehabilitation protocol for the Indian population. The protocol can be practiced in the Indian scenario. This will help to improve the exercise tolerance of the patients after the surgery. The study will recommend the feasible and effective technique for relieving the anxiety and improving the exercise tolerance in CABG patients. This can be implemented as a best practice in reducing anxiety after CABG.

## Introduction

Coronary Artery Disease (CAD) is an epidemic in India which is the result of epidemiological transition, contributed by industrialisation, urbanisation, and lifestyle changes [1]. The inner wall of the artery becomes narrowed and hardened in CAD. Global Burden of Disease (GBD) report 422.7 million people in the world are having CAD, and prevalence is more in Indian population compared to other countries in the same region. World Health Organisation (WHO) and GBD studies reveal that years of life lost (YLLS) and disability adjusted life years (DALYS) raised from 1 to 9–10% in the urban India and <1% to 4–6% [2]. By the end of 20^th^ century CAD contributed 50% of death in developed countries and 25% death in developing countries [3]. The plaque deposit in the artery causes narrowing of the lumen of the artery. Blood supply to the myocardial muscle tissue is compromised in the distal part of occlusion. The heart muscles become unable to contract and the blood supply from the heart is compromised. This leads to unstable angina, myocardial infarction, and sudden death [4]. The risk factors leading to the same is classified as modifiable and non-modifiable. Age, gender, ethnicity, and family history are the factors which cannot be modified. The modifiable factors are hypertension, hyperlipidaemia, diabetes mellitus, obesity, smoking, unhealthy diet, and sedentary lifestyle [5]. Risk factor modification is the mainstay of treatment in the early stages of disease and beneficial as preventive measure [6]. In the initial phases the disease requires conservative medical management [7]. Coronary angiogram is the most widely used diagnostic tool in detecting the severity of stenosis. A stenosed artery above 70% should be repaired surgically, known as coronary artery bypass grafting (CABG)[8]. It is the common surgical technique involving diverting the blood supply to the occluded vessels and replenishing the blood supply of the myocardium. The life expectancy is very high. There are many complications associated with the surgery which may affect the prognosis and quality of life in patients, which accounts 25%. There are physical and mental complications. The physical complications include myocardial infarction, stroke, and even kidney failure and the mental complications include such as mood disorders, fatigue, weakness, stress, anxiety, and depression [9]. Depression and anxiety are the most important factors which badly affect the prognosis of the patient. International Classification for Diseases-tenth edition (ICD-10) depression is defined as the by “low mood and/or anhedonia (loss of interest in activities that once were pleasurable) that lasts for two weeks or more and is accompanied by significant functional impairment and somatic complaints of disturbed sleep, fatigue, body aches, digestive or sexual problems, and negative thoughts”. Defines anxiety as a feeling of apprehension and unease. It has three components. Somatic symptoms include digital tremors, palpitations, and sweaty palms. The physiological component mentions tachycardia, hyperventilation, muscular tension, and an irritable bladder. The cognitive component is the undue fear of something untoward happening. The rate of depression and anxiety is increasing in Indian population due to the socioeconomic factors, fear of death etc. [10] Depression has a long-term effect on CABG patients which accounts for 25% of the population. Anxiety is associated with increased sympathetic activity and reduced parasympathetic activity [11]. Anxiety is a complex psychological disorder which is connected to both physiological and psychological response [12]. This in turn reduces the exercise tolerance. Henceforth alleviation of symptoms of anxiety and depression is utmost important in post CABG patients. And this should be cost effective for the patient, because of the economic concerns which leads to these symptoms. Cardiac rehabilitation is the routine care provided after CABG. It is a multi-disciplinary individualised approach. Various models are available for cardiac rehabilitation, and diverse protocols are being practiced in various countries [13]. Cardiac rehabilitation has an impact of anxiety, which alleviates anxiety [14]. According to ACSM the preferred intensity of phase I cardiac rehabilitation is, Heart rate 120 beats per minute [15]. The inpatient rehabilitation is 3–4 weeks in Austria, and central and eastern Europe [16]. The cardiac rehabilitation protocol in the existing literature is more towards the western culture. The definite protocol for Indian population is adopted from various western countries. So, developing a protocol for the Indian set up is obligatory. Hence the primary objective of the study is to develop the phase 1 cardiac rehabilitation protocol for Indian population. And the same protocol will be validated by various experts in the field and apply this in the patient population and measure the outcome using 6 Minute walk. The same protocol can be used in the current study as the standard treatment protocol. To lessen the anxiety literature suggests the use of pranayama, yogic intervention, includes prolongation and control of breath. Yogic intervention may improve the anxiety among patients undergoing CABG, but lacks literature supporting the similar [17]. Practice of pranayama has an effect on the autonomic system function, and thereby controls anxiety. Pranayama means the control of ‘Prana’ in Indian philosophy, refers to all forms of energy in the universe. Slow and deep breathing technique, “Nadi-shodhana Pranayama” increases parasympathetic activity. But there is a deficiency of literature to prove the effect of “Nadi-shodhana Pranayama” on anxiety in CABG patients [18]. Improving the aerobic capacity can increase peak oxygen consumption and reduce anxiety. Chair aerobics is a form of low intensity activity which can be given for post CABG patients [19]. The literature is deficient to provide evidence of chair aerobics in improving the exercise tolerance and anxiety in patients after CABG. Extensive literature is required prove the effect of “Nadi-shodhana Pranayama” pranayama and chair aerobics in reducing the anxiety and improving the exercise tolerance in the field of CABG.

## Materials and Methods

The trial design is Randomized clinical Trial, outcome assessor blinded double arm trial. The participants will be recruited from department of cardio-thoracic and vascular surgery, Justice K S Hegde charitable hospital.

## Selection Criteria

### Inclusion criteria

CABG patientsAge: 30–80 yearsHADS anxiety cut off score 7Both genders

### Exclusion criteria

Patients with multiple procedures (Eg: CABG+ valve replacement)LVEF < 40%Patients who receive anxiolytics, sedatives, or hypnoticsCardiac FailureHeart TransplantationEssential HypertensionDiabetic Autonomic NeuropathyNeurological DisordersPatients on mechanical ventilator

## Procedure

Interventions: Ethical approval is obtained for the study. Verbal advertisement will be given to the patients of JUSTICE K S HEGDE CHARITABLE HOSPITAL who is undergoing cardiac surgery (CABG) and willing to participate in the study.

Written permission to conduct this study is obtained from the Head of the cardio-thoracic and vascular surgery Department. Informed consent will be obtained from patients. Following the completion of baseline data collection, patients will be allocated into two groups based on computer generated randomization and sequentially numbered, opaque, sealed envelopes (SNOSE).

The study has 2 phases. In first phase the phase 1 cardiac rehabilitation will be validated by experts and then will be applied to patients and obtain the results. In the second phase, the proposed rehabilitation protocol will be applied to the patients in both the groups.

Baseline data will be obtained prior to intervention (including heart rate, respiratory rate, pulse rate, BMI, RPE, 6-minute walk test, HADS, history regarding any medical treatment and other health related conditions).Prior to intervention (on pre-operative day) outcome scores will be taken.Patients will be randomized into 2 groups based on the SNOSE method.

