**Group 1 will receive**

**Yoga therapy (Pranayama)**
The yoga will be delivered by a trained personal. The Nadisodhana pranayama will be delivered once in a day. The vitals will be monitored throughout the procedure and the position will be according to the cardiac rehabilitation.

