**POD 5–7**
1. Alternate heel digs with bilateral arm curl – 16 repetitions2. V- Step with bilateral hammer curls – 16 repetitions3. Lateral step touch with bilateral arm curl – 16 repetitions4. Knee lift – 16 repetitionsThe intensity of the exercises is low and as tolerated by the subject based on RPE Borg’s scale. The total time duration will be 15 minutes.And will receive cardiac rehabilitation phase 1 protocol.All the outcome measures such as HADS, 6MWT and HR, will be taken on preoperative day and on POD 7.Statistical analysis will be done after completing the sample collection. Intention to treat analysis will be done.

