## Sample Size

Based on the mother article, standard Deviation in the intervention group is 6.10 beats per minute [19]. Mean difference for effect size is 0.6483, alpha error 5%, and power 90%. The required samples per group is 50. The total sample size is 100.

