## Results

Intention to treat analysis will be done after completing the sample collection.

Data will be analysed using unpaired t test. p < 0.05 will be considered significant.

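### Allocation is placed straight after the pre-operative baseline, but the first dated arm-specific session is on POD 3–4, so surgery appears to fall between randomisation and treatment

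*Protocol article*

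**What the plan says.** The Procedure section of the protocol article gives the order of events twice. The narrative says "Following the completion of baseline data collection, patients will be allocated into two groups based on computer generated randomization", using sequentially numbered, opaque, sealed envelopes. The list of steps that follows says "Prior to intervention (on pre-operative day) outcome scores will be taken" and, as the very next step, "Patients will be randomized into 2 groups based on the SNOSE method". The outcome schedule under POD 5–7 confirms the timing of the baseline: HADS, the 6-minute walk test and heart rate "will be taken on preoperative day and on POD 7".

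The first dated arm-specific treatment is the chair-aerobics block headed POD 3–4 (Group 2). For Group 1 the article says only "The Nadisodhana pranayama will be delivered once in a day", with no start day.

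The Exclusion criteria list patients on a ventilator, patients taking anxiolytic, sedative or hypnotic drugs, and patients having more than one procedure. No time of assessment is given for any of them.

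The Results section states "Intention to treat analysis will be done after completing the sample collection" and names an unpaired t test. The Abstract has 100 patients randomised; the Sample Size section calculates 50 per group, 100 in total.

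**The concern.** The only trigger named for allocation is completion of a baseline taken before the operation. If the envelope is opened then, the operation and the first post-operative days pass before the first dated session. Some allocated patients may not reach that session.

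The ventilator exclusion sharpens the point. It has little application to someone who has just completed a pre-operative walk test, and it fits mainly the period after surgery. Under the written order, a patient who meets it then already holds an allocation, and the trial has two choices:

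- **Remove the patient.** This is an exclusion after randomisation and conflicts with intention to treat.
- **Keep the patient.** If the patient never starts but has a POD 7 value, the contrast between arms is diluted. If there is no POD 7 value, the patient contributes nothing to a t test on observed values.

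At stake is mainly power, because the sample size carries no reserve. Bias would be added if removals or losses differed between the arms.

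**Working it through.** **1. Order of events, side by side**

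| Step | Timing in the article | Section |
|---|---|---|
| Baseline scores | Pre-operative day | Procedure; POD 5–7 |
| Allocation | Next listed step after baseline; no day given | Procedure |
| Surgery | Not placed in the list of steps | – |
| Ventilator exclusion | No time of assessment | Exclusion criteria |
| First chair-aerobics session | POD 3–4 | Group 2 |
| First pranayama session | No start day | Group 1 |
| Final outcomes | POD 7 | POD 5–7 |

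The natural reading places allocation before surgery. No sentence says so outright.

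**2. The plan's own sample size**

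Inputs from the Sample Size section: "Mean difference for effect size is 0.6483, alpha error 5%, and power 90"%. The figure of 0.6483 reproduces the sample size only if read as a standardised difference d with a two-sided test.

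n per group = 2(z₀.₉₇₅ + z₀.₉₀)² / d² = 2(1.960 + 1.282)² / 0.6483² = 50.0

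This agrees with the stated 50 per group. At d = 0.6483 and SD 6.10 beats per minute, the difference is 0.6483 × 6.10 = 3.95 beats per minute. With the noncentral t distribution, power at 50 per group is 0.894. This is the baseline for the comparisons below.

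The 100 to be randomised equal 2 × 50, so there is no allowance for loss.

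**3. Effect of patients who never start**

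The document gives no rate. I assume 10% and 20%, equal in both arms.

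Noncentrality parameter = d√(n/2), with 2n − 2 degrees of freedom and two-sided alpha 0.05.

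- *Not analysed:* n becomes 50 × (1 − p), and d is unchanged.
- *Analysed, with no treatment contrast among them and an unchanged SD:* d becomes 0.6483 × (1 − p), and n stays at 50.

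| Case | d | n per arm | d√(n/2) | Power |
|---|---|---|---|---|
| Plan | 0.6483 | 50 | 3.24 | 0.894 |
| 10% lost | 0.6483 | 45 | 3.08 | 0.860 |
| 20% lost | 0.6483 | 40 | 2.90 | 0.817 |
| 10% analysed, never started | 0.5835 | 50 | 2.92 | 0.823 |
| 20% analysed, never started | 0.5186 | 50 | 2.59 | 0.728 |

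The normal approximation gives slightly higher values: 0.900 for the plan, 0.868 and 0.826 if lost, 0.831 and 0.737 if diluted. The pattern is the same.

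**4. Bias**

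With equal losses unrelated to arm, the cost is power or dilution, as above. Bias needs removals or losses that differ by arm. The article gives nothing from which to estimate that.

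**The case against.** The strongest reply is that the day of randomisation is never stated. Opening the envelope on POD 3 would satisfy every sentence of the Procedure section, so the fix is compatible with the current text. That is correct, and it limits the claim to the natural reading. It does not remove the point: allocation is twice tied to a pre-operative step and to no later one, so a site following the list would allocate before surgery.

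A reader might also infer four stronger things that the documents do not support:

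- **That the intention-to-treat analysis is already broken.** No sentence removes a randomised patient. Handling of missing POD 7 values is something a condensed article may leave to the full protocol or analysis plan, and naming a t test does not commit the trial to a complete-case analysis.
- **That several exclusions fall after allocation.** Medication history is taken at baseline, so the anxiolytic and sedative criterion can be read as pre-operative screening. Multiple procedures can be judged from the planned operation. Only the ventilator criterion points mainly to the period after surgery, and its timing is also unstated.
- **That both arms start on POD 3.** A start day is documented for chair aerobics only.
- **That staff who know the arm will exclude patients selectively.** The article does not say who applies the criteria. With only the outcome assessor described as blinded, this is possible, but it is speculation.

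It is also fair to say that the power figures for lost patients apply to loss from any cause. Losses after the first session would not be prevented by moving the allocation.

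**Conclusion.** The point holds in a limited form. As ordered in the Procedure section, allocation follows the pre-operative baseline and precedes surgery, while the first dated arm-specific session is on POD 3–4. A patient who met the ventilator exclusion in between would have to be removed, against intention to treat, or kept at the cost of dilution or missing outcomes.

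On assumed rates of 10% to 20%, the cost is 3 to 8 percentage points of power if these patients are lost (0.894 − 0.860 = 0.034; 0.894 − 0.817 = 0.077). It is 7 to 17 points if they are analysed without having started (0.894 − 0.823 = 0.071; 0.894 − 0.728 = 0.166). These figures rest on the assumed rates, on equal rates in both arms, and on reading 0.6483 as a standardised effect. The direction and size of any bias cannot be derived from the document.

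This is a worthwhile, low-cost improvement. It is not a proven failure of the analysis, because the article states neither a pre-operative day of randomisation nor any removal after it.

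**What to change.** State the timing of allocation explicitly:

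1. Keep consent and baseline scores on the pre-operative day.
2. After surgery, re-confirm the existing eligibility criteria, and say when the ventilator criterion is assessed.
3. Open the next envelope immediately before the first arm-specific session, at the same time point for both arms.
4. Analyse every patient whose envelope was opened, in the allocated arm.

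Step 3 needs a defined first session in each arm. The sponsor should therefore reconcile the start days of the two interventions, since only chair aerobics has one at present.

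The cost is a few sentences of text and a brief eligibility re-check for each patient. Some consented patients will have baseline scores but never be randomised, so more than 100 must be consented to randomise 100. The change removes losses before treatment from the randomised comparison. It does not protect against losses between the first session and POD 7.

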**Group 1 will receive**

**Yoga therapy (Pranayama)**
The yoga will be delivered by a trained personal. The Nadisodhana pranayama will be delivered once in a day. The vitals will be monitored throughout the procedure and the position will be according to the cardiac rehabilitation.
**Nadi Sodhana Pranayama**

The individual will be made in Sukhasana (comfortable posture). Patient will be instructed to open the right hand and bend the index finger bent index and middle fingers against the palm. Close the right nostril using the thumb, while the fourth and fifth fingers will used for the left nostril. The patient will be then instructed to place the right thumb against the ala at the end of the nostril to close it and similarly pressed the fourth and fifth fingertips against the left nostril. The procedure will be continued for 15 minutes [20].

**GROUP 2 will receive**

**Chair aerobics**

**POD 3–4**
1. Alternate heel digs with bilateral biceps curl – 8 repetitions2. V- step with bilateral hammer curls – 8 repetitions3. Lateral step touch with bilateral biceps curl – 8 repetitions4. Knee lift – 8 repetitions
**POD 5–7**
1. Alternate heel digs with bilateral arm curl – 16 repetitions2. V- Step with bilateral hammer curls – 16 repetitions3. Lateral step touch with bilateral arm curl – 16 repetitions4. Knee lift – 16 repetitionsThe intensity of the exercises is low and as tolerated by the subject based on RPE Borg’s scale. The total time duration will be 15 minutes.And will receive cardiac rehabilitation phase 1 protocol.All the outcome measures such as HADS, 6MWT and HR, will be taken on preoperative day and on POD 7.Statistical analysis will be done after completing the sample collection. Intention to treat analysis will be done.

## Sample Size

Based on the mother article, standard Deviation in the intervention group is 6.10 beats per minute [19]. Mean difference for effect size is 0.6483, alpha error 5%, and power 90%. The required samples per group is 50. The total sample size is 100.

## Results

Intention to treat analysis will be done after completing the sample collection.

Data will be analysed using unpaired t test. p < 0.05 will be considered significant.

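### The unpaired t test is valid and matches the sample size, but adjusting each outcome for its own preoperative value (ANCOVA) would be more efficient at no cost

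*Protocol article*

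**What the plan says.** The measurement schedule is given in the Procedure, at the end of the Group 2 description: "All the outcome measures such as HADS, 6MWT and HR, will be taken on preoperative day and on POD 7". The Procedure also fixes the order of events: "Following the completion of baseline data collection, patients will be allocated into two groups". Each outcome therefore has a preoperative value recorded before randomisation.

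The analysis is stated twice. The abstract has "The data will be analysed using unpaired t test, p value <0.05 will be considered significant", and the Results section repeats it as "Data will be analysed using unpaired t test", under intention to treat. Neither place names a covariate, a model or a change score. Allocation is computer generated with sealed envelopes, and no stratification on a baseline outcome is described.

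The Sample Size section gives "standard Deviation in the intervention group is 6.10 beats per minute", "Mean difference for effect size is 0.6483", "alpha error 5%, and power 90" per cent, and concludes "The required samples per group is 50".

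**The concern.** A baseline value of the outcome, taken before randomisation, is usually the most useful covariate a trial has. Here it is collected for all three outcomes, but the named test makes either no use of it (POD 7 values) or a rigid use of it (changes from baseline).

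Two things are at stake. The first is precision: the confidence interval for the difference between pranayama and chair aerobics will be wider than the data allow. The second is chance imbalance: with 50 per arm, the groups can differ somewhat at baseline in anxiety, heart rate or walk distance, and the unadjusted estimate carries part of that difference. In addition, the two ways of applying the t test can give different answers from the same data, and their power differs.

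**Working it through.** **Inputs from the protocol article.** Effect 0.6483, SD 6.10 bpm, alpha 5%, power 90%, 50 per group (Sample Size). Baseline is taken before allocation and outcomes are repeated on POD 7 (Procedure).

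**Assumptions.** The correlation r between the preoperative and POD 7 values is not given, so I use 0.3, 0.5 and 0.7. The effect 0.6483 is taken as a standardised difference in POD 7 values, with equal SDs at both times and in both arms. No dropout is allowed for.

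**Step 1: reproduce the sample size.** For an unadjusted two-sided comparison, n per group = 2(1.960 + 1.282)² / 0.6483² = 50.0, which agrees with the stated 50. (The unrounded value is just above 50, so strict rounding up gives 51.) At 50 per group, power is 90.0% by the normal approximation and 89.4% by the exact t calculation. A one-sided test gives 41 per group. Reading 0.6483 as a raw difference in bpm with SD 6.10 gives 1861. Neither reproduces the plan. The target is therefore 0.6483 × 6.10 = 3.95 bpm, and the calculation makes no use of baseline.

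**Step 2: variance of each analysis relative to a t test on POD 7 values.**
- POD 7 values: 1
- Change from baseline: 2(1 − r)
- ANCOVA: 1 − r²

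The change score is worse than POD 7 values alone when 2(1 − r) > 1, that is, when r < 0.5. Since 2(1 − r) − (1 − r²) = (1 − r)² ≥ 0, ANCOVA is never worse than the change score. Since 1 − r² ≤ 1, it is never worse than POD 7 values. The only price is one degree of freedom.

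**Step 3: power at 50 per group, two-sided 5%, noncentral t.** The noncentrality is 0.6483 × √(50/2) / √(variance factor) = 3.2415 / √(variance factor).

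| Assumed r | POD 7 t test | Change-score t test | ANCOVA |
|---|---|---|---|
| 0.3 | 89.4% | 77.4% (factor 1.40) | 92.0% (factor 0.91) |
| 0.5 | 89.4% | 89.4% (factor 1.00) | 96.0% (factor 0.75) |
| 0.7 | 89.4% | 98.5% (factor 0.60) | 99.4% (factor 0.51) |

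The gain of ANCOVA over POD 7 values is 2.6, 6.6 and 10.0 points. Equivalently, 50 per arm analysed by ANCOVA is worth 50/0.91 = 55, 50/0.75 = 67 or 50/0.51 = 98 per arm analysed by a t test on POD 7 values.

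**Step 4: chance imbalance.** The standard error of the baseline difference is √(2/50) = 0.20 SD, so differences up to 1.96 × 0.20 = 0.39 SD lie within the 95% range. A POD 7 t test carries r times the imbalance into the estimate. At the 0.39 limit this is 0.12, 0.20 and 0.27 SD, or 0.7, 1.2 and 1.7 bpm if the baseline SD is also 6.10, against the 3.95 bpm target. Conditional on an imbalance of that size, the type I error is about 8%, 13% and 21%. Averaged over randomisation it remains 5%.

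**The case against.** The strongest reply is that nothing here is wrong. In a randomised two-arm trial the unpaired t test is unbiased over randomisation and holds its 5% level. The trial was sized for exactly this unadjusted comparison, so analysis and sample size agree, and the stated power does not depend on adjustment. All of this stands.

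The size of the benefit is also uncertain. It rests on an r that the article does not give. Surgery lies between the two measurements, and entry on a HADS anxiety cut-off may narrow the baseline range. Both could put r at the low end, where the gain over POD 7 values is small. This stands too.

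Three stronger readings are tempting, and the article supports none of them:
- **The t test gives invalid or biased results.** It does not. The raised type I error in Step 4 applies only conditionally on an unlucky imbalance.
- **The trial is underpowered as planned.** At an effect of 0.5 the POD 7 t test would have about 70% power, but 0.5 is not the planning value. At 0.6483 the power is about 90%.
- **Baseline information is discarded.** This is true only if POD 7 values are compared. If changes are compared, baseline is used, though with a fixed slope.

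Finally, this is a condensed article, and a fuller analysis plan may add adjustment or specify the response. For that reason silence on POD 7 values versus changes is not itself held against the plan. The test, however, is not left open: it is named twice, so a recommendation to improve it is fair.

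**Conclusion.** The point holds as an efficiency improvement to a stated method. The t test is valid, but under either way of applying it ANCOVA does at least as well. At the trial's own planning effect with 50 per arm, ANCOVA raises power from 89.4% to between 92.0% and 99.4% relative to POD 7 values, over assumed correlations of 0.3 to 0.7. The lower end is a gain of only about 2.6 points. The clearest avoidable loss would come from a change-score t test with a low correlation: at r = 0.3 power falls to 77.4%, which is 14.6 points below ANCOVA.

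These figures depend on the assumed r and on reading 0.6483 as a standardised POD 7 difference. The planning effect is for heart rate. The article gives none for HADS or the 6-minute walk test, so for those outcomes only the variance factors carry over, each at that outcome's own correlation.

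**What to change.** For each outcome (HADS, heart rate and 6-minute walk test), make the main analysis a linear model of the POD 7 value on treatment arm plus that outcome's own preoperative value. Report the adjusted mean difference between arms with its 95% confidence interval and p value. Keep the unpaired t test on POD 7 values as a sensitivity analysis.

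This also settles the response variable: with the preoperative value in the model, the treatment estimate is the same whether the response is the POD 7 value or the change.

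The cost is one sentence in the analysis section, ideally written before outcome data are examined. It needs no new measurements, no extra patients and no change to the sample size, which was calculated without adjustment and stays adequate for the planned effect.
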